## **6.6 Study completion**

After the final 24 month follow-up visit patients will return to the standard care pathway and continue standard care follow-ups, which will be arranged at the time of discharge. Patients in the study are unlikely to require any further intervention once the research is finished. If there were any complications due to the use of Strattice™, the patient may need further treatment or an intervention to remove the Strattice™. In any such cases, patients would have direct access to clinical services as per standard care. If the complication developed during the study period, patients would not be discharged until it is suitably resolved, even if that period was to extend beyond the planned study period.

Patients will be able to contact the study team or clinical care team at any point during or after the study with any questions or concerns. Patients will also be given contact details for an independent patient group.

## **6.7 Study withdrawal**

Patients are free to withdraw consent and end participation in this study at any time without having to give a reason and without current or future care being in any way affected. Patients should contact study team if they wish to end participation.

Participation in this study may be ended by the clinician or the sponsor without patient consent at any time in the following circumstances:

- Investigator thinks it is necessary for your health or safety;
- Patient has not followed study instructions;
- The sponsor has ended the study.

If a patient experiences disease progression or metastases they would receive whatever treatment is deemed necessary by the clinical care team, including further treatment or surgery, but this would not usually be a reason for study withdrawal. Any adjuvant therapy including radiotherapy, chemotherapy and immunotherapy are not an exclusion criteria would not be a reason for study withdrawal. If a patient experienced reconstructive failure or any complications which required the removal of Strattice™, patients would be withdrawn from the study and would be treated according to standard care.

If the patient decides to withdraw from the study, or is withdrawn, the study data collected prior to withdrawal may still be processed along with other data collected as part of the study but no future data will be collected. A withdrawal form in the CRF would need to be completed.

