### **5.4 Statistical Methods**

The main endpoint to be analyzed is the proportion of unplanned reoperations after the initial breast reconstruction. The difference in proportions between the two groups will be presented as a difference in proportion together with a 95% confidence interval. Differences will be tested using Fishers Exact Test. Logistic regression will be used to take into account possible confounding factor.

364  
365 The sample size calculation is made with respect to the primary endpoint, which is to  
366 compare the number of unplanned surgical procedures (unanticipated) between IBR  
367 using full muscle coverage without ADM vs. IBR with ADM using partial muscle  
368 coverage (group B) over the study period of two years. The power calculation is based  
369 on a reoperation rate of 60% in the non-ADM group and a reoperation rate of 30% in  
370 the ADM group. The follow-up time is 24 months from the primary operation.

371  
372 To detect a statistical difference between the two groups a total number of 98 patients -  
373 i.e. 50 patients in each arm – is needed, if the significance level is set to 5% and the  
374 power in the study to 80%. To account for a loss to follow-up, a total of 120 patients will  
375 be recruited in the study.

376

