## 6 OUTCOMES AND ASSESSMENT OF EFFICACY

### 6.1 Primary outcome measures

The primary endpoint of this study is the number of unplanned/ unanticipated surgical breast procedures. Other endpoints in the trial will be secondary.

As reoperation rates are a relatively objective measure of surgical intervention required to attain and maintain acceptable aesthetics in implant based reconstructions, it will serve as a good primary endpoint for the study. See Appendix 1 for guidance on defining reoperations.

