## 15 APPENDICES

### 15.1 Appendix (1): Definition of reoperations

As reoperation rates are a relatively objective measure of surgical intervention required to attain and maintain acceptable aesthetics in implant based reconstructions, it serves as a good primary endpoint for the study.

An unplanned reoperation in the study is defined as any subsequent surgical procedure including, but not limited to the following:

- a. Reoperation caused by complications (e.g. implant removal or evacuation of hematoma or seroma) or due to cosmetic reasons, or implant exchange for other reasons (implant exchange from permanent expander to anatomical gel is considered as an unplanned reoperation).
- b. Capsulectomy/ capsulotomy
- c. Any secondary autologous reconstruction
- d. Lipofilling

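### Withdrawal for reconstructive failure or Strattice removal also ends data collection, so follow-up for unplanned operations stops because of the outcome itself

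*Protocol*

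**What the plan says.** Section 6.7 (Study withdrawal) makes withdrawal the rule after two kinds of event: "If a patient experienced reconstructive failure or any complications which required the removal of Strattice™, patients would be withdrawn from the study". Its last paragraph covers both patients who withdraw and patients who are withdrawn. Data from before that point may still be used, "but no future data will be collected". The same section keeps patients in the study after disease progression, metastases or adjuvant therapy, so leaving after a failed reconstruction is a specific choice.

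The primary endpoint appears in two forms. Section 6.1 has a count: "The primary endpoint of this study is the number of unplanned/ unanticipated surgical breast procedures". The synopsis likewise compares the number per patient. Section 5.4 has a proportion, tested with Fisher's exact test: "The main endpoint to be analyzed is the proportion of unplanned reoperations after the initial breast reconstruction". Section 5.4 sets the follow-up at 24 months from the primary operation.

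Appendix 1 lists what counts as an unplanned reoperation. Item (a) includes implant removal for complications, and item (c) is "Any secondary autologous reconstruction".

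Section 6.6 (Study completion) says of complications arising during the study that "patients would not be discharged until it is suitably resolved, even if that period was to extend beyond the planned study period".

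**The concern.** The event that takes a patient out of the study is a bad result on the primary endpoint. The operations most likely to follow it, such as a secondary autologous reconstruction, are further events on the same endpoint, and section 6.7 stops anyone recording them. This is loss of follow-up caused by the outcome, and it is written into the protocol. A statistical analysis plan can decide how to treat missing data but cannot supply the missing operations.

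The secondary outcomes in section 6.2 are affected in the same way: total procedures, complications after the failure, cost over 24 months, quality of life and aesthetic result. The cost outcome matters in particular. Section 4 says that the trial may support routine use of the product if its cost is offset by fewer later operations or visits. Salvage surgery that is never recorded is missing from that calculation.

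The two arms are also not exposed to the rule in the same way. Group A receives no Strattice, so withdrawal for Strattice removal can happen only in Group B.

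**Working it through.** **The plan's own figure.** Section 5.4 assumes 60% and 30%, 5% significance (taken as two-sided) and 80% power.
- Uncorrected n per arm = [1.96·√(2·0.45·0.55) + 0.8416·√(0.24 + 0.21)]² / 0.30² = 41.97, so 42 (84 in total).
- With continuity correction, n = (41.97/4)·[1 + √(1 + 4/(41.97·0.30))]² = 48.4, so 49 per arm and 98 in total.

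This matches the stated 98. The present point does not change it. Recruiting 120 leaves room for a loss of 22/120 = 18.3% from 98, or 20/120 = 16.7% from the 100 implied by 50 per arm. The protocol does not say which patients make up that loss.

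**Which events are lost.**
1. Implant removal for a complication is an event (Appendix 1a) and will normally be what section 6.7 calls reconstructive failure or what accompanies Strattice removal.
2. Appendix 5 (vi) has implant and ADM removed together, so many Strattice removals are also reconstructive failures. The part specific to Group B is Strattice removal without failure.
3. After withdrawal nothing is collected, so later events under Appendix 1 (a) to (d) are not seen. No other section restores collection.

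**Count endpoint.** Let f be the share of an arm withdrawn and m the mean number of further operations each would have had by 24 months. The arm's mean is too low by f·m. The protocol gives neither value; the range below is assumed.

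| f | m = 0.5 | m = 1 | m = 2 |
|---|---|---|---|
| 5% | 0.025 | 0.05 | 0.10 |
| 10% | 0.05 | 0.10 | 0.20 |
| 20% | 0.10 | 0.20 | 0.40 |

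For 60 patients in an arm (120/2) this is 60·0.025 = 1.5 to 60·0.40 = 24 unrecorded operations. The bias in the difference between arms is the difference of the two products. For example, 15% in B and 5% in A with one further operation each gives 0.15 − 0.05 = 0.10 operations per patient.

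**Proportion, triggering operation recorded and patient kept.** The patient is already an event. Later operations cannot change that, so there is no bias.

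**Proportion, withdrawn patients dropped as lost.** If every failure is an event and the true rate is p, the analysed rate is (p − f)/(1 − f). Take p = 45% in both arms (assumed; the midpoint of 60% and 30%).
- A, f = 5%: 0.40/0.95 = 42.1%.
- B, f = 15%: 0.30/0.85 = 35.3%. The apparent difference is 6.8 points where none exists.
- B, f = 20%: 0.25/0.80 = 31.3%. The apparent difference is 10.9 points.
- f = 10% in both: 0.35/0.90 = 38.9% in each, no difference.
- f = 15% in A and 5% in B: the 6.8 points favour Group A.

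The exact probability that Fisher's test shows a significant ADM benefit, with 50 analysed per arm, is 1.7% with no loss, 7.3% for 5% against 15%, and 15.0% for 5% against 20%. With 10% in both (54 per arm) it is 1.6%.

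**The case against.** The best defence concerns the tested analysis. Section 5.4 powers and tests a proportion. Section 11.1 requires adverse events and any surgical intervention to be recorded, and section 6.7 allows data from before withdrawal to be used. A patient whose removal operation is on the case report form is therefore already counted. Nothing in the protocol says she is dropped, and the handling of withdrawn patients commonly belongs in a statistical analysis plan. This stands: bias in the Fisher comparison is conditional. It does not help the count endpoint or the 24-month secondary outcomes.

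Three stronger readings are tempting, and the protocol does not support them.
- A reader might infer that the failures leave mainly from the ADM arm and that the rule favours ADM. No failure rate by arm is given, reconstructive failure applies to both arms, the two triggers overlap, and section 3 calls the complication data conflicting.
- A reader might infer that section 6.6 contradicts section 6.7. Section 6.6 speaks of discharge and access to clinical services, not of data collection. A patient can be withdrawn from the study and still not be discharged. The wording is awkward and should be clarified, no more.
- A reader might infer that the clause "Patient has not followed study instructions" is exclusion after randomisation. It says that participation may be ended, and it is not tied to one arm. It does stop further data collection if used, so the same amendment should cover it.

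Finally, after implant loss or autologous conversion, a reconstruction questionnaire or photograph may not mean what it was meant to. That calls for a decision on how to analyse it, and does not justify stopping collection altogether.

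**Conclusion.** The point holds as a fault in the protocol as written. Section 6.7 ends data collection because of an event that is normally a primary-endpoint event. The count of unplanned procedures and the 24-month secondary outcomes are then incomplete for the patients who did worst.

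The size cannot be derived from the documents. Under the assumed range the undercount is 0.025 to 0.40 operations per patient in an arm. The direction is also unknown: the arm with the larger product of failures and later operations looks better than it is.

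For the proportion in section 5.4 there is no bias if the triggering operation is recorded and the patient stays in the denominator. If such patients are treated as loss to follow-up, the bias at equal true rates favours whichever arm has more failures; 42.1% against 35.3% is one assumed example. The false-positive figures rest on the same assumption and should not be read as the expected behaviour of the trial.

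The point should be settled before patients are withdrawn under this rule, because operations not recorded at the time may not be recoverable.

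**What to change.** Amend section 6.7 so that reconstructive failure, Strattice removal or non-adherence does not end data collection. Specifically:
- Follow all randomised patients to 24 months for operations, complications and costs and, where applicable, quality of life and photographs, unless the patient withdraws consent to data collection.
- Analyse them in their allocated arm.
- Count the triggering operation and every later operation that meets Appendix 1.
- State how questionnaires and photographs are handled after implant loss or autologous conversion.
- Clarify how the discharge wording in section 6.6 relates to section 6.7.

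This concerns data collection only. It sets no rule for treatment and leaves the sample size unchanged.

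The cost is a change to the protocol and consent wording, plus slightly more data collection. Section 6.5 describes the follow-up appointments to 24 months as current standard care, so no new visits are needed.

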### **6.3 Randomisation**

After signing and dating the Informed Consent Form (ICF) the patient can be entered into the study and randomized. Randomization occurs via a database system at Regional Cancer Center (RCC) within Karolinska Institute, Sweden. In this system the inclusion and exclusion criteria will be automatically verified before patients are randomized. An outline of instructions for randomization can be found in Appendix 2. Full details of how to randomize a patient and access the randomization system will be provided by Karolinska Institute to local sites upon study commencement.

Upon randomization each patient will be allocated a unique Study Identification (ID) number which will be used to identify patients throughout the trial. This Study ID should be recorded on all study documents including the ICF and all CRF's and Questionnaires.

Patients will be randomized to either Group A (without Strattice™) or Group B (with Strattice™). Patients should be informed of their allocation promptly and a letter sent to their GP to inform them of their participation and treatment allocation.

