## 15.5 Appendix(5): Defining a surgical infection

- i. Signs suggesting infection, such as redness and/ or edema of skin, should be confirmed by elevated levels of C-Reactive Protein (CRP) to qualify as an infection.
- ii. In case of wound dehiscence/ wound breakdown and/ or oozing, bacterial culture is taken.
- iii. Also to be recorded is whether there is skin dehiscence only, muscle/ implant exposure and/ or skin flap necrosis. **If signs of skin flap necrosis, any expander in place should be deflated.**
- iv. In case of localized redness/ erythema of the skin overlying ADM, without elevated levels of CRP and LPK, the event is to be regarded as local inflammation, and should be treated with Non Steroid Anti-Inflammatory (NSAID) drugs.
- v. **Any seroma formation in the ADM group should be treated aggressively with ultra sound guided percutaneous drainage and patient put on prophylactic antibiotics for 7 days.**
- vi. If surgical intervention with removal of implant is decided, both implant and ADM should be removed. If regarded as an infection, three levels of treatment can be defined:
  1. Oral antibiotics
  2. Intravenous antibiotics with patient treated at ward in hospital
  3. Infection requiring implant removal

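### Reconstructive failure or Strattice removal ends data collection, so later counted procedures and late secondary outcomes are lost for failed reconstructions, and one of the two triggers exists only in Group B

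*Protocol*

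**What the plan says.** Protocol section 6.7 (Study withdrawal) first lists reasons for which the clinician or sponsor may end participation. It then adds a rule that is not discretionary: "If a patient experienced reconstructive failure or any complications which required the removal of Strattice™, patients would be withdrawn from the study". For anyone who withdraws or is withdrawn, "no future data will be collected", while "the study data collected prior to withdrawal may still be processed along with other data collected as part of the study". The same section says that disease progression or metastasis would not usually be a reason for withdrawal.

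Section 6.6 (Study completion) says of a complication arising during the study that "patients would not be discharged until it is suitably resolved, even if that period was to extend beyond the planned study period".

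On the endpoint, section 6.1 (Primary outcome measures) says "The primary endpoint of this study is the number of unplanned/ unanticipated surgical breast procedures". Section 5.4 (Statistical Methods) analyses a proportion with Fisher's exact test over 24 months. Appendix 1 counts implant removal for a complication as an unplanned reoperation, and also "Any secondary autologous reconstruction". Appendix 5, item vi, says that when the implant is taken out, "both implant and ADM should be removed".

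**The concern.** An unplanned operation that ends the reconstruction is what the primary endpoint is meant to capture, and it is also what takes the patient out of the trial. Salvage surgery after a failed implant, such as a flap reconstruction, is a counted event under Appendix 1 but falls after withdrawal and is not collected. Later complications, total procedures, 24-month cost, quality of life and photographs are lost for the same patients.

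The two triggers are not symmetric. Reconstructive failure is undefined and can occur in either arm. Strattice removal can occur only in Group B. If Group B patients meet the triggers more often, more of their later burden disappears. This matters for the trial's stated use: section 4 says the results may support routine use if the product's cost is offset by fewer later operations. A SAP cannot repair this, because the data will not exist.

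**Working it through.** **Inputs from the protocol (section 5.4).** Reoperation rates of 60% (no ADM) and 30% (ADM), 5% significance, 80% power, 98 patients needed, 120 recruited, 24 months of follow-up.

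**Assumptions.** Two-sided testing, as sidedness is not stated. Failure or removal rates f are not given: I take 5% in A and 10-15% in B, with equal and reversed rates as checks. Each failure leads to m = 1 or 2 later counted procedures. Sixty per arm are randomised, with no other losses.

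**1. The plan's own figure.** Without continuity correction, n per arm = [1.96·√(2·0.45·0.55) + 0.842·√(0.6·0.4 + 0.3·0.7)]² / 0.30² = 42. With continuity correction it is 49, so 98 in total, which matches the protocol.

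**2. Count of procedures.** Procedures lost per arm = 60·f·m; shift in the mean difference = (f_B − f_A)·m.
- 5% vs 10%: A loses 3-6 procedures and B 6-12; shift 0.05·1 to 0.05·2 = 0.05-0.10 per patient.
- 5% vs 15%: A loses 3-6 and B 9-18; shift 0.10·1 to 0.10·2 = 0.10-0.20 per patient.
- 5% in both arms with the same m: shift 0, although both means are understated.

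**3. Yes/no endpoint, removal recorded and counted.** The patient is already an event and later losses cannot change that. The rates stay at 60% and 30%. Under equal true rates, Fisher's test rejects in 3.2% (at 60%) or 3.4% (at 45%) of trials, as it would without the rule.

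**4. Yes/no endpoint, withdrawn patients dropped.** With every failure being an event, the shown rate is (p − f)/(1 − f). For example, A: (0.60 − 0.05)/0.95 = 57.9%; B: (0.30 − 0.10)/0.90 = 22.2%. Differences below come from unrounded rates.

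| True A / B | Failure A / B | Shown A vs B | Difference (points) | Fisher rejection |
|---|---|---|---|---|
| 60% / 30% | 5% / 10% | 57.9% vs 22.2% | 35.7 (true 30) | not needed |
| 60% / 30% | 5% / 15% | 57.9% vs 17.6% | 40.2 (true 30) | not needed |
| 60% / 30% | 10% / 5% | 55.6% vs 26.3% | 29.2 (true 30) | not needed |
| 45% / 45% | 5% / 5% | 42.1% vs 42.1% | 0 | 3.0% |
| 45% / 45% | 5% / 10% | 42.1% vs 38.9% | 3.2 (true 0) | 4.8% |
| 45% / 45% | 5% / 15% | 42.1% vs 35.3% | 6.8 (true 0) | 9.4% |

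**5. Yes/no endpoint, removal not captured and the patient kept as a non-event.** The spurious difference is f_B − f_A: 5 points at 5% vs 10% (rejection about 6%) and 10 points at 5% vs 15% (about 16%).

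**6. Which of cases 3 to 5 applies?** The protocol does not settle it. Use of earlier data is permitted rather than required, and section 6.7 does not say whether withdrawal takes effect before or after the removal operation.

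**The case against.** A reader might infer that the worst outcomes are cut out of the primary comparison. The documents do not support that. The planned test is on a proportion, the removal is itself an Appendix 1 event, section 11.1 (Adverse Events) has surgical interventions recorded in the CRF, and earlier data may be used. No passage says that withdrawn patients are excluded, and analysis sets are normally a SAP matter. This stands: the figures in steps 4 and 5 show what is left open, not what is planned.

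A reader might also infer that the error must favour ADM. That is not shown. There are no failure rates by arm, section 3 calls the complication data conflicting, and loss of an implant in Group A would ordinarily count as reconstructive failure. Because Appendix 5 pairs implant and ADM removal, the Strattice trigger largely overlaps with failure. Equal rates give no spurious difference, and 10% in A with 5% in B runs slightly against ADM. This stands too.

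Nor does section 6.6 plainly contradict 6.7. It can be read as discharge from clinical care, with no bearing on study data. The two sections are unclear together and need reconciling.

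None of this reaches the core. The stop in data collection is automatic and tied to the outcome, and the procedure count and late secondary outcomes lose data however the yes/no endpoint is coded.

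**Conclusion.** The concern holds for the procedure count and for the secondary outcomes after failure: section 6.7 creates informative loss of follow-up, with one trigger confined to Group B. Under the assumed 5% versus 10-15% failure and 1-2 later procedures each, about 0.05-0.20 procedures per patient are hidden in ADM's favour. Size and direction rest on those assumptions, and the direction requires the triggers to be met more often in Group B, which the documents do not establish.

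For the yes/no primary endpoint the conclusion is conditional. It is unbiased by this rule if the removal is recorded and counted, but the protocol does not guarantee that. The weakness should be corrected in the protocol because data not collected cannot be recovered at analysis.

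**What to change.** Amend section 6.7 without altering clinical care:
- Remove reconstructive failure and Strattice removal as reasons for withdrawal from follow-up.
- Continue all assessments to 24 months in both arms unless the patient withdraws consent to data collection. Take reoperations from hospital records where that consent allows.
- Count the removal and every later procedure in the randomised arm.
- State that data collected before a withdrawal will be analysed.
- Define reconstructive failure identically for both arms.
- Reconcile section 6.6 with 6.7, saying whether discharge there means from the study or from clinical care.

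The cost is a short amendment and a few extra CRFs. Study visits already coincide with routine appointments where possible (section 6.5, Schedule of Events). The sample size stays at 98 evaluable and 120 recruited.
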